#### Provisions for posttrial care {30}

Participants in the waitlist control condition receive access to the Internet-based treatment after a waiting period of 3 months.

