#### Composition of the data monitoring committee, its role, and reporting structure {21a}

An independent Data Safety and Monitoring Board (DSMB) has been established which will meet once a year. This DSMB is independent of all investigators and the funding agency, and no member of the DSMB has direct involvement in the conduct of the study. The DSMB is composed of three researchers familiar with the area of the study. The DSMB will monitor recruitment, the number of dropouts, and all adverse events including study withdrawals.

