#### Adverse event reporting and harms {22}

During the trial, symptom deterioration and suicidality will be closely monitored. Participants in the CETA-I condition who score 1 on the suicide item will be invited to complete the safety module that includes follow-up questions. Participants who indicate immediate plans and means, or previous attempts, will be called and guided through the rest of the safety module. Participants who indicate no immediate plans or means and no previous attempts complete the safety module on their own. Participants who score 2 or above on the suicide item will be called directly and guided through the safety module. (2) Participants will be encouraged to communicate potential adverse effects to their online therapists or the PIs. (3) Online therapists will be required to report adverse events immediately to their supervisor and the PIs. 4) The PI will decide if an adverse event must lead to treatment termination. All such cases will be documented and considered for the analyses of the study results.

At post-assessment, we will collect the negative effects caused by the treatment systematically [57]. Participants will complete the NEQ and are encouraged to further note all adverse events that occurred during treatment in an open-ended question. In addition, other markers indicative of adverse events, like hospitalization, as assessed by FIMPsy, and deterioration rates, will be published.

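### Apart from hospitalisation and questionnaire deterioration, adverse events are collected through treatment-bound routes, so those counts cannot be compared between CETA-I and waitlist

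*Protocol article*

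**What the plan says.** Item 22 (Adverse event reporting and harms) names these routes:

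- Spontaneous reports: "Participants will be encouraged to communicate potential adverse effects to their online therapists or the PIs".
- Required onward reporting: "Online therapists will be required to report adverse events immediately to their supervisor and the PIs".
- Systematic collection: "At post-assessment, we will collect the negative effects caused by the treatment systematically". This is then specified: "Participants will complete the NEQ and are encouraged to further note all adverse events that occurred during treatment in an open-ended question".
- Further markers: "other markers indicative of adverse events, like hospitalization, as assessed by FIMPsy, and deterioration rates, will be published".
- Suicide item, first step: "Participants in the CETA-I condition who score 1 on the suicide item will be invited to complete the safety module". The step for higher scores is written for participants in general.

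Item 21a gives the monitoring board a wide remit: "The DSMB will monitor recruitment, the number of dropouts, and all adverse events including study withdrawals". Item 30 fixes the control condition: "Participants in the waitlist control condition receive access to the Internet-based treatment after a waiting period of 3 months".

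Item 12 limits only the 3-month and 6-month follow-ups to the active condition. Table 2 schedules the HSCL-25 and PCL-5 at baseline, week 5 and post, the health-care use questionnaires (FIMA and FIMPsy) at baseline and post, and the NEQ at post. It attaches no arm restriction to any of them. Items 20a, 20b and 22 state no between-arm test of adverse events.

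**The concern.** The randomised waitlist is what allows harm from treatment to be separated from events that would have happened anyway. That matters here, because the participants are distressed at entry and CETA-I includes a trauma exposure module (Table 1). The separation works only if both arms are asked the same thing over the same period.

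As item 22 is worded, a crisis or an episode of self-harm without hospital admission can reach the record in CETA-I through the therapist, through the NEQ or through the open question. On the waitlist the same event is recorded mainly if the participant contacts the PIs. The monitoring board and the final report would then hold adverse-event counts that were not gathered in the same way in the two arms.

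**Working it through.** **Step 1. Which routes reach an untreated waitlist participant before the primary endpoint?**

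| Route (item 22) | CETA-I | Waitlist |
|---|---|---|
| Report to online therapist | yes | no: therapist feedback follows completed sessions (item 11a), and there are none while waiting |
| Therapist's duty to report onward | yes | no equivalent reporter named |
| Report to the PIs | yes | yes |
| NEQ | yes | not excluded by Table 2, but it concerns effects of a treatment not yet received |
| Open question at post | yes | as worded, it covers a treatment period that does not exist |
| FIMPsy hospitalisation | yes | yes (baseline and post) |
| Deterioration rates | yes | yes (the questionnaires are scheduled in both arms) |

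The cost-utility comparison in item 20a also needs health-care use from the waitlist, which supports reading FIMPsy as collected in both arms. The marks for the weekly items (including suicidal ideation) are absent from the text available, so nothing is inferred about whether the waitlist completes them.

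**Step 2. What unequal capture could do.** The protocol gives no adverse-event risk and no capture rate, so there is no plan figure to reproduce, and all risks and capture rates below are assumptions. With the same true risk p in both arms and capture probabilities c_T (CETA-I) and c_W (waitlist):

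spurious risk difference = p × (c_T − c_W).

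With c_T = 0.9, in percentage points:

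| p | c_W = 0.9 | 0.6 | 0.3 | 0 |
|---|---|---|---|---|
| 5% | 0 | 1.5 | 3 | 4.5 |
| 10% | 0 | 3 | 6 | 9 |
| 20% | 0 | 6 | 12 | 18 |

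Example in counts, using the planned allocation in item 14 (75 and 56), p = 10% and c_W = 0.3: 75 × 0.10 × 0.9 = 6.8 expected recorded events in CETA-I, against 56 × 0.10 × 0.3 = 1.7 on the waitlist, with no true difference.

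**Step 3. Is the direction certain?** No, for two reasons.

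- Item 14 assumes attrition of 40% in CETA-I and 20% on the waitlist. A question asked only at post can reach at most 60% and 80% of those randomised. If waitlist participants did answer it fully, a 10% risk in both arms would be recorded as 0.10 × 0.6 = 6% and 0.10 × 0.8 = 8% of those randomised, a difference of 2 points in the opposite direction.
- Item 12 places post at the last session or week 12, and item 11a allows 6 to 16 weekly sessions. The CETA-I observation period may therefore be shorter or longer than the waitlist's 12 weeks.

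**Step 4. What the two arm-neutral markers can support.** Expected completers are 75 × 0.6 = 45 and 56 × 0.8 = 44.8, in line with the 44 per arm in item 14. With 45 per arm, the 95% half-width for a risk difference is 1.96 × √(2p(1 − p)/45). This gives 9.0, 12.4 and 16.5 percentage points at p = 5%, 10% and 20%. A comparison is possible but imprecise.

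**The case against.** The best defence is that the plan already has harms data for both arms. Hospitalisation and deterioration rates are to be published and are scheduled at baseline and post without arm restriction. The PI route is open to everyone, and participants are encouraged to use it. The HSCL-25, which also picks up suicidal ideation, is given in both arms at week 5 and post. The NEQ is by nature an instrument about treatment, so having no counterpart in an untreated group is no fault in it. No between-arm test of spontaneous reports or NEQ scores is planned, so no invalid comparison is prescribed. Finally, this is a condensed article, and the real item may be worded differently from its description here.

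Most of this stands, and it limits the point. A reader might infer that harms cannot be compared at all, that the bias certainly runs against CETA-I, or that a several-fold false excess is to be expected. The documents support none of these. Two markers are arm-neutral, the direction is open (working, step 3), and any ratio merely restates the capture rates assumed.

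The defence does not close the gap. Hospitalisation finds only events that led to admission, and deterioration is a change in a questionnaire score. Neither records self-harm or a crisis without admission as an event. Encouragement to contact the PIs is not equivalent to a scheduled question plus a therapist with a duty to report. Nor is this just detail left to a fuller document: the article states both the attribution and the period, and both are tied to treatment.

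**Conclusion.** The point holds in a limited form. As item 22 is worded, therapist reporting, the NEQ and the open question have no counterpart for waitlist participants before the primary endpoint. Adverse events other than FIMPsy hospitalisation and questionnaire deterioration are therefore ascertained unequally, and counts from these routes cannot be compared between arms.

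The counts are likely to be higher in CETA-I, because that arm has more routes. This is not certain, given the higher attrition assumed there and the unequal observation periods. The figures in the working show the mechanism and a range under stated assumptions; they are not estimates for this trial. The conclusion rests on the article's description of the question being faithful to the actual item. The primary efficacy analysis is unaffected.

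**What to change.** 1. Reword the open-ended question to *any adverse event since randomisation (or since the last assessment)* and ask it identically in both arms at the existing post-assessment, optionally also at week 5.
2. Use a common window of 12 weeks from randomisation in both arms. Where the CETA-I post-assessment does not fall at week 12, dated events or a week-12 answer are needed to keep that window.
3. State that any between-arm harms comparison uses only this item, FIMPsy hospitalisation and deterioration rates.
4. Report NEQ results and therapist-reported events descriptively for CETA-I.

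The cost is one reworded online item, an amendment approved by the ethics committee and reported in the registry (item 25), and slightly more events to document on the waitlist. The change does not remove the difference in attrition, so response to the item should be shown by arm. If the full protocol already contains a neutral item, correcting the description in item 22 is enough for step 1.

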#### Frequency and plans for auditing trial conduct {23}

The Data Safety and Monitoring Board will audit trial conduct (including recruitment rates and frequency of adverse events) in their yearly meeting.

#### Plans for communicating important protocol amendments to relevant parties (e.g., trial participants, ethical committees) {25}

Any amendments to the study protocol would have to be approved first by the Medical School Berlin Ethics Committee. If approved, these changes would have to be reported in the trial registry. Finally, any amendments would be reported in the trial paper.

##### Dissemination plans {31a}

Trial results will be published in a peer-reviewed journal. The results will also be presented at scientific conferences. A popular science summary of the results will be posted online for laymen and study participants. An anonymized data set as well as statistical code used to analyze the data will be published in a data repository on OSF.

## Discussion

The planned trial aims to develop and evaluate a scalable treatment option for Arabic and Farsi-speaking participants with common mental disorders. We hypothesize that the Internet-based CETA treatment will be more effective than no treatment. The trial will result in important insights about how acceptable this form of treatment is to the target population; how feasible it is for online therapists, supervisors, and patients; and finally how effective it is to decrease the mental health load for patients. We will tailor treatment to the individual patient, an approach that has been successfully realized in previous transdiagnostic online trials [72, 73]. However, the specific tailoring process, including several sources of information (questionnaires, interviews, patients’ problem descriptions), is innovative and has not been tested in an Internet-based setting before. The same applies to the adaptation of the intervention during the treatment process. We know only one Internet-based pilot study that tested just-in-time adaptations for patients with insomnia [74]. Thus, the planned trial not only will provide very relevant data for the undertreated population of refugees but also it will add to the growing field of personalized Internet-based interventions.

### Limitations and conclusion

The planned design is associated with some limitations. First, even if our primary outcome measure is well validated within Arabic and Farsi-speaking populations, we include several questionnaires within our extensive assessment battery that have not yet been translated into Arabic or Farsi. Within a related subproject, careful translations will be performed adhering to WHO standards. However, the results of these questionnaires should still be interpreted with caution as psychometric properties will be largely unknown for the target population. Second, primary and secondary outcomes rely on self-report alone and we do not include a clinician or observer judgment.

Furthermore, acting as a strength and limitation at the same time, we will not apply any exclusion criteria regarding length of stay or asylum status for our patients. This might result in a very heterogeneous group of patients, facing different life situations and different mental health challenges. We will, of course, carefully assess asylum-related factors and evaluate their impact on treatment uptake and outcome. Still, interpretation of (potentially inconsistent) results will be more difficult. We chose these wide inclusion criteria for two reasons. First, it will make it easier to meet our recruitment goal. And second, it will increase external validity. The ultimate goal of the planned project is to help implement efficacious treatments for the undertreated population of refugees and other migrants. By including all participants independent of their time and reason to immigrate to Germany and also by testing the online treatment in other treatment settings in related subprojects, we hope to make a significant contribution to closing the gap between treatment needs and uptake in the vulnerable group of refugees and migrants in Germany.

### Trial status

Participant recruitment starts in November 2023 and is expected to be completed by spring 2025.

## Data Availability

After the publication of trial results, a de-identified data set, as well as analysis code, will be made publicly available on the research data repository OSF.

## Abbreviations

ADIS: Anxiety and Related Disorders Interview Schedule
AUDIT: Alcohol Use Disorder Identification Test
CBT: Cognitive behavior therapy
CBT-SQ: Cognitive-Behavioral Skills Questionnaire
CETA: Common Elements Treatment Approach
CETA-I: Common Elements Treatment Approach-Internet-based version
CSQ-I: Client Satisfaction Questionnaire-Internet-based interventions
DIPS: Diagnostisches Interview für Psychische Störungen (Diagnostic Interview for Mental Disorders)
DSM-5: *Diagnostic and Statistical Manual of Mental Disorders-5*
DSMB: Data Safety and Monitoring Board
DUDIT: Drug Use Disorder Identification Test
EQ-5D-5L: European Quality-of-Life 5-Dimensions 5 Level
FIMA: Fragebogen zur Inanspruchnahme von medizinischen und nicht-medizinischen Versorgungsleistungen im Alter (Questionnaire on the Utilization of Medical and Nonmedical Services for the Elderly)
FIMPsy: Fragebogen zur Inanspruchnahme von medizinischen und nicht-medizinischen Versorgungsleistungen bei psychischen Störungen (Questionnaire on the Utilization of Medical and Nonmedical Services for Mental Disorders)
GCTR: German Clinical Trial Registry
GSE: General Self-Efficacy Scale
HSCL-25: Hopkins Symptom Checklist-25
ITT: Intention to treat
NEQ: Negative Effects Questionnaire
OSF: Open Science Framework
OSSS: Oslo Social Support Scale
PCL-5: PTSD Checklist for DSM-5
PHQ-4: Patient Health Questionnaire-4
PMLD: Post-Migration Living Difficulties Scale
PTSD: Post-traumatic stress disorder
RCT: Randomized controlled trial
WAI-I: Working Alliance Inventory-Internet-based interventions
WHO: World Health Organization
